#### Enrollment

Researchers will publish recruitment information through the hospital website, designate dedicated personnel to consult patients and their families via telephone and video connections, conduct preliminary screening based on the exclusion criteria (Table 1), and recommend qualified patients to bring complete relevant examinations, test data, and cases to the hospital. In the outpatient clinic, qualified neurosurgery clinicians will further evaluate and diagnose the patients. Eligible patients will be enrolled, and the researcher will give full informed consent and sign an informed consent form. The evaluators will collect surgical baseline data based on the case report form (CRF). The patient will be admitted to the hospital 1 week before the operation. After admission, general preoperative examinations and tests will be completed, including an electrocardiogram, chest X-ray, hematuria and stool routine, coagulation screening, blood type identification, biochemistry, and eight preoperative items. Then, the patient will be evaluated by professional evaluators. The main evaluation contents will include an assessment of motor function, mental behavior, quality of life, past disease history, and related treatment drugs and measures. Finally, the day before the operation, the examiner will arrange for the patient to undergo a brain MRI examination. The examination results will be burned into a CD and handed over to a dedicated person for safekeeping. On the day of the operation, the surgical planning system (ELEKTA) will be introduced for preoperative planning, including electrode implantation paths and treatments (44).

**Table 1 tab1:** List of inclusion and exclusion criteria.

Inclusion	Exclusion
(1) Meet WHO or International diagnostic criteria for post-stroke hemiplegia;	(1) Glasgow Coma Scale (GSC) score below 15, Minimum Mental State Examination (MMSE) assessment for dementia indicated, suffering from mental disturbance and unable to cooperate with examination or treatment.
(2) The first unilateral supratentorial ischemic stroke, the condition is stable after acute treatment of ischemic stroke, the course of disease is ≥1 year, and participate in 2 evaluations (screening and baseline) before enrollment.	(2) Motor and sensory disturbances are not induced by stroke, nor by previous ischemic stroke, but stroke induced by trauma, brain tumor, etc.
(3) Diagnosed by professional physicians combined with brain CT or magnetic resonance imaging and other imaging techniques;	(3) Serious comorbidities, such as malignant tumors, primary heart, liver, kidney or hematopoietic system diseases.
(4) Between the ages of 18 and 80, male or female	(4) History of cognitive impairment, mental disorder, drug abuse, drug allergy, and alcoholism.
(5) The responsible lesion in the unilateral white matter area indicated by cranial CT or MRI	(5) Previous craniotomy, thrombectomy and thrombolysis.
(6) Relevant sequelae such as limb dysfunction after stroke, accompanied by unilateral limb motor dysfunction, proved to be right-handed by standardized examination.	(6) Possess a pacemaker, metal stent, plate, or implant susceptible to electrical impulses in the body (pacemaker or defibrillator, baclofen pump, deep brain stimulator, Ventricular shunts, shrapnel, etc.).
(7) There is obvious motor disorder, FMA motor function score is between 50 and 84;	(7) Pregnant or breast-feeding or have a recent birth plan.
(8) Perfect clinical data	(8) Clinical data are perfect.
(9) Stable medical and physical condition with adequate nursing support and appropriate medical care in the patient’s home community.	(9) Congenital or acquired abnormalities of lower extremities (affecting joints and bones).
(10) The patient himself or voluntarily signs the informed consent and is willing to cooperate with relevant treatment.	(10) Registration of investigators, their family members, employees, and other dependents.
Withdrawal criteria	(11) Severe joint contractures cause loss or limitation of lower limb activities.
(1) After the start of the clinical study, it is found that the subjects do not meet the case inclusion criteria;	(12) Blood system diseases with increased risk of bleeding during surgical intervention.
(2) There is no data after enrollment;	(13) Participate in another study drug study within 30 days before and during this study.
(3) Subjects have poor compliance and have never used the experimental treatment plan;	(14) Unable to complete the basic process, or difficult to maintain compliance and follow-up.
(4) Those who seriously violate the experimental protocol.	
Termination criteria	
Continuation of the study may harm the relevant rights and interests of a certain number of subjects	

#### Interventions

The process of MLR-DBS for post-stroke hemiplegia is in Figure 3. All individuals in the study will receive bilateral stereotactic implantation of intracranial leads under general anesthesia. The patient will be installed with a Leksecl-G directional device under general anesthesia in the operating room and undergo MRI positioning scanning in the MRI room during the operation. Default CnF coordinates will be calculated from the MRI brainstem landmarks to target the brainstem normalized coordinates and use the diffusion tract map to ensure we target the medial, superior cerebellar, and central peduncles, within the area demarcated by the lid (Figure 4). Before DBS lead placement, microelectrode recording and test stimulation will be performed to assess intraoperative physiology and rule out potential side effects that may require repositioning of the lead. First, electrophysiological mapping of CNF will be performed. Microelectrodes will be precisely inserted along predefined trajectories, directed toward the CNF, and connect the neuromodulation system and manual actuators to the stereotaxic device. The center of this area shows neuronal responses to imaginary walking, which stimulates passive and active lower body movements while the patient performs a series of motor tasks with their lower body suspended from the operating table. As this study is the first to investigate DBS of CNF in patients with post-stroke movement disorders, there are no guidelines for optimal stimulation parameters. However, comparable evidence accumulated from preclinical studies in various animal models suggests that low-frequency stimulation (≤50 Hz) at moderately wide pulse widths (200–1,000 μs) may be possible due to the evolutionary conservation of the MLR in mammalian species properties (45). Therefore, we first stimulated with increasing voltage at 20 Hz, 400 μs, 2.0–4.5 V pulse width, and then adjusted the frequency and pulse width based on individual intraoperative behavioral responses. Intraoperative MRI and postoperative CT will be used to determine whether the electrode insertion position will be deviated and whether the operation will be completed after checking for accuracy.

**Figure 3 fig3:**
[figure not shown]
Graphic of DBS delivery during therapy sessions. During the in-clinic rehabilitation session, for each movement effort, the clinician/therapist generates the DBS pulse via a push button connected to a laptop computer. A Wireless Transmitter, attached to the laptop, triggers the patient’s implanted pulse generator to deliver the DBS pulse.

**Figure 4 fig4:**
[figure not shown]
A schematic representation of the MLR localization. MLR localization was performed in combination with preoperative imaging, stereotactic map of human brain and related literature.

#### Randomization

The 62 patients will be enrolled in the group undergoing deep brain electrode implantation. The 62 patients will be randomly divided into two groups at a ratio of 1:1 using a simple random grouping method, with 31 patients in the DBS group and the control group. First, random numbers will be automatically generated by the OpenClinica clinical trial data management platform to achieve centralized randomization. When a new patient meets the inclusion and exclusion criteria and signs the informed consent form, each research center can apply for the patient’s randomization number after filling in the patient’s basic information in OpenClinica. The random numbers will be automatically issued by the system, and only one coordinator in each center has access. All patients included in the study will receive DBS implantation after baseline assessment and were then randomly divided into two groups in a 1:1 ratio: DBS treatment group and control group. The former will start electrical stimulation treatment 1 month after the operation. Specialists will assess the patient’s recovery status through the remote rehabilitation system every week and guide rehabilitation training and electrical stimulation treatment. The latter will receive the same rehabilitation training under the face-to-face guidance of experts, except for the power-on (sham stimulation, the power-on stimulation parameter was 0). Experts will evaluate the patient’s recovery and adjust rehabilitation strategies every week in the outpatient clinic. The study is blinded to participants, scale raters, and data analysts. Allocation information will be kept in opaque, sealed envelopes by a designated person not involved in the study, thus ensuring the concealment of random assignment.

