## Methods and analysis

### Study design

The trial is a multicenter, prospective, double-blind crossover randomized controlled trial (RCT). The overall process is in Figure 2. In this study, we will include 62 moderate to severe post-stroke hemiplegia patients who had stable disease after 1 year of conservative treatment in multiple neuro medical centers in the General Hospital of the People’s Liberation Army of China et al. All patients included in the study will undergo deep brain electrode implantation. They will be randomly postoperatively divided into a DBS group and a control group, with 31 patients in each group. 1 month after surgery, the DBS group will be given electrical stimulation treatment, while the control group will undergo routine observation. Following up in the 3rd and 6th months after surgery. After the follow-up, all patients will stop electrical stimulation treatment for 2 weeks. After the 2-week washout period, the control group will start electrical stimulation treatment, and the DBS group will continue observation. Outpatient follow-up in the 6th and 9th months after surgery. After the follow-up, all patients will undergo electrical stimulation treatment. Observe for a long time. The leading outcome measure of follow-up is the pre-and post-change score on the Fugl-Meyer Assessment Upper Extremity Scale (FMA-UE). In addition, we will follow up on changes in the secondary outcomes of balance function, neuropsychiatric behavior, Post-stroke Spasticity, fall risk, activities of daily living, and quality of life.

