**Figure 2 fig2:**
[figure not shown]
Brief flowchart of the entire study with draw. For patients whose electrode is not implanted in the ideal position in CT review after DBS implantation, the device can be temporarily left off, and the follow-up of clinical trials is excluded, and relevant conventional rehabilitation means can be actively given. The health status of patients can be observed at any time, and regular follow-up can be conducted. When all clinical trials are over, the effect of DBS treatment can be observed. If the effect of DBS treatment is better than that of the traditional control group, the electrode position should be adjusted again and DBS treatment should be performed again.

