### Methods

#### Sample size

This study is a randomized, double-blind, active sham stimulation control design, and statistical experts determined that the sample ratio between the DBS group and the control group was 1:1. A review of the literature revealed that subjects’ upper limb FMA scores improved by an average of 7 points. Since this study was based on the changes in the mean FMA before and after DBS treatment, based on literature data, the mean FMA before DBS treatment was 21.92 ± 6.30, and the mean FMA after DBS treatment was 35.42 ± 12.23. This study is designed as a difference test to determine whether the mean of the DBS group (u1) is different from the mean of the control group (u2) (41, 42). The assumptions are as follows: H0: u1 − u2 = 0, H1: u1 − u2 ≠ 0. The two-sided significance level was 5%, the statistical power was 90%, and the dropout rate was 20% (43). The total sample size required for this study was calculated by PASS V.15 sample size calculation software to be 48 patients, with 24 people in each group. According to the possibility of electrode implantation deviation and other special circumstances leading to a lose, we included 62 patients, 31 in each group.

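### The article lets the randomisation number be issued at consent but elsewhere puts randomisation after surgery, and does not place the off-target-electrode exclusion before or after allocation

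*Protocol article*

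**What the plan says.** **Timing of randomisation.** The Randomization section of the protocol article says: "When a new patient meets the inclusion and exclusion criteria and signs the informed consent form, each research center can apply" for the patient's number. By the Enrollment section, consent precedes admission, and admission is a week before surgery. Further down, the Randomization section says that patients "will receive DBS implantation after baseline assessment and were then randomly divided into two groups in a 1:1 ratio". The Study design section agrees with that later sentence: "They will be randomly postoperatively divided into a DBS group and a control group". The abstract (Methods/design), the Discussion and the Advantages section also put randomisation after surgery, and the last two present this as protection against an unblinded surgeon. Table 2 has a single column for allocation and surgery together, ahead of the post-surgery column.

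**Exclusion after implantation.** For electrodes found out of position on CT after implantation, the Figure 2 caption says "the device can be temporarily left off, and the follow-up of clinical trials is excluded". The Sample size section allows for this: "According to the possibility of electrode implantation deviation and other special circumstances leading to a lose, we included 62 patients", against a calculated 48.

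**Other removals.** The withdrawal criteria in Table 1 cover patients later found ineligible, patients with no data after enrolment, patients who comply poorly and never used the treatment, and "Those who seriously violate the experimental protocol".

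**Blinding.** The Blind method section first lists all operators as blinded, then says the operating doctor cannot be.

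**Method.** Allocation is made "using a simple random grouping method", with 31 patients stated for each group.

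**The concern.** A patient removed before allocation costs only sample size. A patient removed after allocation leaves a comparison that randomisation no longer fully protects. Which of these applies to off-target electrodes depends on when the allocation is fixed and known relative to the CT check, and the article gives two incompatible times. Because excluded patients leave trial follow-up, their later outcomes are not collected, so no choice of analysis set could bring them back.

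The Discussion and Advantages sections also rest part of the blinding argument on randomisation coming after surgery. A number issued at consent, to which a coordinator at each centre has access, would weaken that argument.

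**Working it through.** **1. The timing statements side by side.**
- Number available before surgery: one sentence in Randomization.
- Randomisation after surgery: abstract, Study design, a later sentence in Randomization, Discussion, Advantages (five places).
- Randomisation after the CT check: stated nowhere.
- Who judges CT position, and whether blind to allocation: stated nowhere.

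So even the majority reading, after surgery, does not settle whether the CT exclusion falls before or after allocation. The headcount does not help: all 62 are said to be implanted and split 31/31, yet the 62 already contains the reserve for electrode deviation.

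**2. Reproducing the plan's 48.** Inputs from Sample size: two-sided 5%, 90% power, 20% dropout, a 7-point improvement, pre-treatment SD 6.30. The article does not say which difference and SD entered the software, so this pairing is an assumption.
- Normal approximation: n per arm = 2 × (1.960 + 1.282)² × 6.30² / 7² = 17.0, rounded up to 18.
- With the t distribution, 18 per arm gives 89.9% power and 19 gives 91.5%, so 19.
- Dropout: 19 / 0.8 = 23.75, so 24 per arm and 48 in total. This matches.
- A difference of 35.42 − 21.92 = 13.5 with SD 12.23 also leads to 19, then 24 per arm.

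**3. Size of the reserve.**
- Above the calculated number: 62 − 48 = 14, and 14/62 = 22.6%.
- The 48 already contains 20% dropout (2 × 19 = 38 evaluable), so the whole allowance is (62 − 38)/62 = 24/62 = 38.7%. Hence 22.6% is not a ceiling on losses.
- If all 14 reserve losses fell before allocation, 48 would be randomised and only the 20% dropout would remain as post-randomisation loss.

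**4. Worst-case illustration, resting on assumptions that are not in the article.** Suppose the lowest 22.6% of a normally distributed outcome were lost from one arm only. That arm's mean moves by φ(z)/(1 − 0.226) = 0.388 SD, where z is the 22.6th percentile of the standard normal and φ its density. This is 0.388 × 6.30 = 2.4 points, or 0.388 × 12.23 = 4.7 points, against an effect of 7. It is extreme: at the CT check no outcome has been observed, so exclusion could not follow the outcome this closely. Losses unrelated to arm and outcome move the difference by nothing on average.

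**5. Simple randomisation of 62, read as a coin flip per patient.**
- P(31/31) = C(62,31)/2⁶² = 0.101.
- P(36/26 or more uneven) = P(|n₁ − 31| ≥ 5) for Binomial(62, 0.5) = 0.253.

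**The case against.** The text leans heavily one way: five places put randomisation after surgery, two of them as a deliberate safeguard. The contrary sentence says when a centre may apply for a number, not when the allocation is revealed, and the same section keeps allocation in sealed opaque envelopes. A number drawn at consent and opened after surgery would reconcile everything. This is a fair reading, but the article does not state it, and it still leaves the CT check unplaced.

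A reader might infer that about a fifth of randomised patients could be dropped selectively. The article does not support that:
- The 14 is a reserve, not an expected loss.
- Off-target patients are lost after randomisation only if allocation precedes the CT check.
- Both arms receive the same bilateral implantation and neither is stimulated before 1 month, so electrode position cannot depend on arm. Selection needs a CT judge who knows the allocation, and nothing says that the unblinded operating doctor makes this decision.
- The withdrawal criteria carry no figure. They cover poor compliers only if these never used the treatment, and do not say that anyone leaves the analysis. Analysis sets may be defined in a plan that is not shown.

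On the secondary point, simple random grouping with 31 per group may mean a fixed-size list, which gives 31/31 by construction. A 36/26 split also costs little: the standard error rises by a factor √(1/36 + 1/26) / √(2/31) = 1.013. Both objections stand, so this part is minor. Neither reading balances centres.

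**Conclusion.** The contradiction on timing is real and lies within one section. It matters because the article attaches an exclusion from follow-up to a check made after implantation, without saying on which side of allocation it falls or whether it is blind. Under the consent-stage rule, those exclusions are avoidable post-randomisation losses and the safeguard claimed in the Discussion and Advantages sections is lost. If allocation follows the CT check, the electrode problem disappears.

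The article's only indication of size is the reserve of 14 of 62 (22.6%), covering electrode deviation and other special circumstances together. Bias from the CT exclusions requires knowledge of allocation by whoever judges the CT. The conflicting statements on operator blinding leave that possible, but do not establish it. This should be corrected; it does not show that the comparison is biased.

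The simple-randomisation point is secondary: exact 31/31 has probability about 10%, and 36/26 or more uneven about 25%, if allocation is by coin flip.

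**What to change.** - State one allocation point: after the postoperative CT position check and before the 1-month switch-on. Neither arm is stimulated before then. The weekly rehabilitation contacts differ by arm (remote or outpatient) and their start is not dated, so allocation should precede those too.
- If a number must be generated earlier, say that it stays concealed until that point. At the least, have CT position judged by someone blind to allocation, and name that role.
- Reconcile the two statements on operator blinding, and say whether 62 is the number implanted or the number randomised.
- Follow all randomised patients for outcomes and analyse them in their assigned sequence. Reconcile the Table 1 withdrawal criteria with this. It concerns data collection and analysis only, not any rule on treatment.
- Replace simple randomisation with permuted blocks stratified by centre in OpenClinica, using small blocks of varying size to limit predictability.
- The Discussion says the study is under way. For patients already enrolled, record the dates of number issue, of the CT check and of disclosure of the allocation, so that any post-randomisation exclusions can be identified.

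Cost: protocol wording and a change to the OpenClinica configuration, with no added visits or patients.

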#### Blind method

To ensure study quality, all operators, therapists, patients, evaluators, and analysts will remain blinded to assignments and interventions until data collection, analysis, and video recording are completed. During video recording, patients wear surgical caps to conceal the data collection time point. These videos will be uploaded to a central unit and scored by two neurologists, without knowledge of whether the patient is receiving DBS treatment. The data administrator will label the groups as A and B for analysis. However, to safeguard patient safety, the operating doctor cannot be blinded to provide timely treatment in case of emergency. Overall, patient safety is our utmost priority (44).

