
### Data analysis

All data analysis will based on IBM SPSS Statistics 25.0, describing the total score of each scale at each follow-up and the change from baseline at each visit after treatment. Measurement data using mean ± standard deviation to describe. Count data Use numerical values (%) to describe, and use group t-test or Wilcoxon to compare between groups according to the characteristics of the data. Intra-group comparisons were performed using rank sum-test, paired t-test or paired signed rank-test. For comparisons of pre-and post-treatment change values based on baseline general information, appropriate multivariate analysis models were used to correct for the effects of confounding factors or covariates based on the data situation. The single-item count data of each scale used the chi-square test or the exact probability test, and the grade data used the Wilcoxon rank sum test. A paired rank sum test and repeated measures analysis of variance were used to analyze the changes in score data within the group before and after treatment. The effectiveness measurement index is the improvement rate of each clinical scale at different follow-up times = (scale score at each postoperative time point − preoperative score) / preoperative score * 100%. A score improvement rate > 25% is considered effective. Safety observation indicators are all postoperative adverse reactions, including surgery-related adverse reactions, device-related adverse reactions, and stimulation-related adverse reactions. The type, number of cases, occurrence time, treatment measures, and prognosis of adverse events are recorded. The incidence of adverse events is defined as the number of patients in which it occurs divided by the number of all patients, and an adverse event rate of less than 5% is considered safe.

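### As most naturally read, the Randomization section has the DBS group guided remotely and the control group face to face, so the between-group FMA-UE contrast mixes stimulation with mode of supervision

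*Protocol article*

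**What the plan says.** All in the protocol article:

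- **Randomization, DBS group.** The section names the two groups and then takes them in turn. The first starts stimulation one month after surgery. The next sentence has specialists check recovery "through the remote rehabilitation system every week and guide rehabilitation training and electrical stimulation treatment".
- **Randomization, control group.** "The latter will receive the same rehabilitation training under the face-to-face guidance of experts, except for the power-on"; sham means that the output is set to 0. The next sentence has experts evaluate recovery and "adjust rehabilitation strategies every week in the outpatient clinic".
- **Blinding.** Randomization states: "The study is blinded to participants, scale raters, and data analysts". Blind method goes further: "all operators, therapists, patients, evaluators, and analysts will remain blinded to assignments and interventions". Outcome videos are to be "scored by two neurologists, without knowledge of whether the patient is receiving DBS treatment".
- **Comparison.** Sample size sets up a test of "whether the mean of the DBS group (u1) is different from the mean of the control group (u2". Data analysis lists between-group tests and adds: "Intra-group comparisons were performed using rank sum-test, paired t-test or paired signed rank-test".
- **Second period.** Study design swaps stimulation between the groups after a two-week washout. It does not say how rehabilitation is supervised after the swap.

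**The concern.** Supervised rehabilitation is aimed at motor function, which is what the primary outcome measures. It is delivered after randomisation, so randomisation does not balance it if its route is set by arm. In the first period every stimulated patient would then have remote guidance and every control in-person guidance. Route and stimulation would coincide exactly, and no covariate adjustment could separate them in the between-group contrast. A difference in FMA-UE could come from stimulation, from supervision or from both, and a true effect of stimulation could be hidden if in-person guidance works better.

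Route is also something that patients and therapists can see. Anyone who knows the scheme could infer the arm from it.

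**Working it through.** **1. What is tied to which arm.**

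| Sentence in Randomization | Route | Tied to an arm by |
|---|---|---|
| Weekly recovery check and guidance | Remote system | Its position after the DBS sentence, and its mention of stimulation treatment |
| Rehabilitation training | Face to face | Explicit wording (control group) |
| Weekly evaluation and adjustment | Outpatient clinic | Its position after the control sentence only |

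Weekly review is described twice, by two routes, within a former/latter structure. Had both groups had both routes, there would be no reason to attach face-to-face guidance to the controls. Type of training and weekly frequency match; route does not.

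**2. Does another section equalise the route?** Study design says only that controls are observed. Data management makes outpatient visits the main method, but for follow-up assessments. The Figure 3 caption shows in-clinic sessions with stimulation, but gives no schedule and does not say which groups attend. None of these sets one route for weekly guidance.

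**3. What each contrast estimates.** Let τ be the effect of stimulation, r and f the effects of remote and face-to-face guidance, δ = r − f, and π the period effect. Assume no carry-over and the same r and f in both periods.

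- Period 1, DBS minus control: (τ + r) − f = τ + δ.
- *Route stays with the randomised group.* DBS-first patients, on minus off: (τ + r) − (r + π) = τ − π. Control-first patients: (τ + f + π) − f = τ + π. The average is τ, so δ cancels. The period 2 between-group contrast is (τ + f) − r = τ − δ, which is still biased.
- *Route moves with stimulation.* On minus off is τ + δ − π in one sequence and τ + δ + π in the other. The average is τ + δ, so the within-patient contrast is confounded as well.

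The cancellation in the first case is called large, not complete, because guidance may accumulate and δ may differ between periods.

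**4. Illustration only.** The protocol's own figure reproduces. A two-sample t-test (two-sided 5%, 90% power) with a difference of 7 and SD 6.30 needs 19 per group; 19 / 0.8 = 23.75, so 24, and 48 in total. A difference of 13.5 (35.42 − 21.92) with SD 12.23 also gives 19, then 24. The protocol gives no value for δ, so |δ| of 1 to 3 points is assumed here, with 31 per group and no dropout. The non-centrality is the net difference divided by SD × √(2/31), that is, by 1.60 at SD 6.30 and by 3.11 at SD 12.23.

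- Stimulation has no effect: the 5% test rejects in 9% to 45% of trials at SD 6.30, and in 6% to 16% at SD 12.23.
- True effect 7, SD 6.30, controls helped by 1 to 3 points: power falls from 99% to between 96% and 69%.

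These figures show sensitivity to an assumed shift. They do not estimate the bias.

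**The case against.** The strongest reply is that this is loose drafting. Only the face-to-face clause names an arm. The same sentence says that training is the same apart from stimulation. Therapists and patients are to be blinded, which fits badly with a deliberate difference in route, and Figure 3 shows stimulated patients treated in clinic. This stands in part: the allocation of routes is a reading, and if stimulated patients attend regular clinic sessions the difference is smaller. But stating that only stimulation should differ does not make the routes equal, and centres that follow the text would make them differ.

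Masked video scoring limits rating bias. It cannot remove a real effect of supervision on motor function.

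The crossover is a fair defence under one condition, namely that the route stays with the randomised group and the analysis uses the within-patient contrast. The protocol does not settle the first, and its stated hypothesis compares group means.

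The unblinding argument needs someone to know the scheme, and the article does not say that patients are told it. The Discussion already concedes that active stimulation is likely to be detected. Route is a possible further cue, no more.

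A reader might infer that the trial will favour DBS. The documents do not support a direction: better guidance in person would work against DBS. A reader might also count weekly contacts to size the problem or the saving from a change. That count measures neither bias nor cost, because no end date for the contacts is given and in-clinic sessions may remain in both groups.

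**Conclusion.** The point holds in conditional form, with medium confidence. On the most natural reading, supervision route differs by arm, and the between-group FMA-UE contrast then estimates stimulation plus route. Size and direction are unknown. A reader might go on to infer that the crossover as a whole is invalid; that is not supported, because whether the within-patient contrast is affected depends on the unstated route in period 2. The conclusion rests on two assumptions: that the sentences follow the order of the groups, and that no unshown text sets a common route. It is a cheap improvement, worth making on either reading: it removes a confounder and a possible unblinding cue if the text is literal, and prevents centres from creating them if it is not.

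**What to change.** Amend the Randomization section to state that weekly recovery checks, rehabilitation guidance and programming contacts (sham at output 0) use the same route, frequency and content in both groups and in both periods. Using the existing remote system for all is the practical choice, and the Introduction already names commuting as an obstacle to adherence. Hold any in-clinic sessions of the Figure 3 kind on the same schedule in both groups, with sham sessions when stimulation is off. In the analysis, flag patients already treated under the old route.

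Cost: an amendment in a trial that the Discussion describes as under way, possibly less in-person contact for controls, and a mix of old-route and new-route patients. No net saving in visits should be assumed.
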